### Recruitment Procedure

We will select 10 to 12 PHCs in health districts with multiple skin NTDs coendemicity as our study site and allocate them equally into intervention and control arms. Targeted patients will include individuals with skin diseases identified through skin surveillance activities and who access the selected PHCs for diagnosis and treatment of their conditions. Local health care providers will be recruited purposively from our study site. A total of 44 local health care providers, including nurses and community health workers, will be selected to participate in the study; the number per PHC will be based on the population of the catchment area of the PHC. All participants will be enrolled formally only after signing the informed consent form.

### Intervention

#### Phase 1: Development and Improvement of the eSkinHealth App and the Platform

The current prototype of the eSkinHealth app is made up of six primary functions, which include (1) patient ID and demographics, (2) symptom list, (3) symptom basic information, (4) history list, (5) record of the day, and (6) photo list (Figure 1). The content of these screens has been developed based on our previous field surveys [1] and from the research team’s experience in managing dermatological patients. We have built-in some special features within each screen (Figure 2). The screen with the patient ID and demographics allows for entry of basic information, automatic calculation of BMI, and assessment of the patients’ nutritional status. The nutritional status could be an important risk factor/indicator for several skin conditions, including wound healing. Patients may present with multiple skin conditions, and this could be organized and managed under the screen of the symptom list. In the screen with the symptom basic information, important information on diagnosing a skin disease is provided as a drop-down choice, so it is not missed and easy to enter. If patients are to return to the clinic, the evolution of their symptom could be seen at a glance in the screen with the history list, allowing comparison with previous symptoms. Lastly, physical examination results of a 1-day visit could be entered in the screen with the record of the day, and clinical photos could be taken, which will be automatically organized in the screen with the photo list. A unique function that we included in our tool is the itchiness and pain visual scale whereby patients themselves could touch the screen and indicate how they are experiencing these sensations each time.

This app is not a disease-specific tool and is fit for use for a wide range of skin conditions with two algorithms: one for nonulcerative skin diseases and another for wounds, a very common manifestation of the skin in LMICs but with different follow-up approaches as compared to other skin conditions. Other special features of the app include patient information security using QR codes. Patients are issued a QR code at their first visit. When they present it to a local health care provider with a device running the eSkinHealth app during follow-up visits, it allows access to their records, making their health records secure and portable.

We will conduct a series of opinion hearings, including expert panel reviews, weekly team meetings, and in-depth interviews and focus group discussions with target end users. In addition, we will develop a web-based platform to manage the case and to have a consultation with a remote health care provider. The app will sync with the platform and will include the following additional functionalities: data overview, search function, and graphical display of data.

**Figure 1 figure1:**
[figure not shown]
Algorithm in the eSkinHealth app.

**Figure 2 figure2:**
[figure not shown]
Sample screens of the eSkinHealth app.

#### Phase 2: Pilot Trial to Evaluate the Usability of eSkinHealth

We will conduct a 3-month pilot trial to evaluate the usability of eSkinHealth. Local health care providers in the intervention arm will be provided with a tablet with eSkinHealth installed and a Wi-Fi router, and will be trained on how to use the app by study staff. All local health care providers, irrespective of intervention or control arm, will be provided with a training on the screening and management of important skin diseases. We will then apply a questionnaire survey to investigate the usability of the eSkinHealth app [22]. As for usability, the questionnaire surveys will use the System Usability Scale (SUS) developed and validated by Brooke [23,24]. We will conduct the SUS over a 3-month follow-up with repeated assessments at baseline, the midpoint (6 weeks), and the end of the study (12 weeks). Furthermore, we will conduct several in-depth interviews with:

Users (ie, local health care providers) to gather feedback on their experience, perceived value, and willingness to use the eSkinHealth app, and identify the obstacles and challenges faced in the implementation of the mobile appsPatients (parents or caregivers for children) to assess their willingness to have eSkinHealth used during their consultation (or consultation of their children)District officers and program managers to collect and further examine their opinions about the feasibility and advantages and disadvantages of adopting the eSkinHealth app by local health care providers already involved in the delivery of primary health care

#### Phase 3: Pilot Trial to Evaluate the Effectiveness of eSkinHealth for Early Diagnosis and Case Management

The same local health care providers as in phase 2 will participate. They will register patients suspected of the targeted skin NTDs (Buruli ulcer, leprosy, yaws, scabies, and lymphatic filariasis) who provide an informed consent during active case finding and during consultation at PHC throughout the trial period on the eSkinHealth app platform. Clinical data at the time of initial identification and at every follow-up visit until cure will be entered in eSkinHealth, including the photos of their skin lesions. The data will be uploaded when connected to the internet and integrated into one database server. When in need of a consultation, a request will be sent to remote experts/dermatologists in Côte d’Ivoire or members of the global health dermatology community, and advice or a clinical confirmation will be provided. As for the control arm, they will diagnose and manage the cases with skin NTDs as usual following the national standard guidelines. Reporting cases from the control arm will be done by paper-based reports using the consultation registry of the Ministry of Health and the skin NTD reporting forms of the World Health Organization [25].

### Outcome Measurement

For phase 2, we will use a validated questionnaire (SUS). The outcome measurement is an average of the SUS score. Bangor et al [26] found that the SUS was highly reliable (α=.91) and useful over a wide range of interface types [27,28]. The SUS consists of 10 statements with responses in the form of a 5-point Likert scale (eg, 1: strongly disagree; 5: strongly agree). According to Bangor et al [27], a SUS score above 68 would be considered above average. In addition, a SUS score above an 80 is considered excellent and places the product in the top 10% of products tested [29]. We will use the French language version of the SUS. We will assess the usability at baseline, the midpoint (6 weeks), and the end of the study (12 weeks). In-depth interviews will be performed at the end of the study.

For phase 3, differences in case numbers diagnosed and the early detection and follow-up between the intervention group (diagnosis with the app) and the control group (usual diagnosis) will be measured as the primary outcome of this study.

### Data Collection

All survey data will be obtained by study staff. We will use validated and study-specific instruments for data collection in person at enrollment, the midpoint (week 6), and the end point (week 12); the SUS and semistructured interviews will assess the usability of the app and portal. For storage of data, we have been using the Amazon S3 (Simple Storage Service) of the Amazon Web Service server, which offers a safe, secure, highly durable storage infrastructure with continuous backups, regulated under the US Health Insurance Portability and Accountability Act. Only the study team and those registered with the eSkinHealth app system (eg, nurses at primary health care clinics) will have access to data. All paper documentation including the signed consent forms will be stored in a secure cabinet, and access will be available only to the study staffs approved by the institutional review board (IRB).

### Statistical Analysis

#### Sample Size Estimation

As for patients, a convenience sample (N=1320) of participants eligible to participate in this pilot study will be recruited. Sample size calculations were not conducted, as this is a pilot trial. The sample size of 1320 was selected based on the number of participants that could be conveniently recruited and tested within the pilot study time frame. From our previous studies, the average number of patients that got registered to the eSkinHealth app was approximately 10 per PHCs per month.

As for local health care providers, 44 local health care providers (22 local health care providers per group) will be recruited for this study. A power analysis was performed using G*Power 3.1.9.6. An estimated medium effect size of Cohen *f* 0.25 was used to determine the sample size needed for a repeated-measures multivariate analysis of variance (RMANOVA) with three time points and two groups. With 95% power (1 – ß), a sample size of 44 local health care providers is needed to detect the hypothesized medium-sized effects on the various outcomes. This RMANOVA would uncover all large- and medium-sized effects but no small-sized effects.

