#### Data Analysis

Statistical analyses will be performed using Stata software (version 16, StataCorp). The threshold for statistical analyses will be set at *P*<.05 in a 2-tailed test. We will summarize the baseline data by group assignment using descriptive statistics: means and SDs will be used for continuous data with normal distribution, medians and IQRs for skewed data, and percentages for categorical data. Our primary outcome, number of diagnosed and early detection will be assessed by mix model analysis of variance, with intervention assignment as a between-group factor and time as a within-subject factor. As for continuous data, we will compare the data between control and intervention group using the *t* test or the Wilcoxon Mann-Whitney test. For categorical data, we will compare the data using the chi-square test.

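### The 95% power of 44 providers applies to the within-provider effects (group-by-time or time), not to all medium effects: a medium difference between arms has about 51%

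*Protocol article*

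**What the plan says.** Under Sample Size Estimation, the protocol article states that "44 local health care providers (22 local health care providers per group) will be recruited for this study". The basis is given as "An estimated medium effect size of Cohen *f* 0.25 was used to determine the sample size needed"; the test is a multivariate analysis of variance with repeated measures, two groups and three time points, calculated in G*Power. The result is that "With 95% power (1 – ß), a sample size of 44 local health care providers is needed to detect the hypothesized medium-sized effects", and the claim extends to the various outcomes. The paragraph then concludes: "This RMANOVA would uncover all large- and medium-sized effects but no small-sized effects". It does not name the effect that was powered.

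Two other sections bear on this. Data Analysis sets the significance level ("The threshold for statistical analyses will be set at *P*<.05 in a 2-tailed test"). It plans a model with assignment as the between-group factor and time as the within-subject factor, and it lists t tests or Wilcoxon Mann-Whitney tests for comparing the arms on continuous data. Recruitment Procedure allocates 10 to 12 primary health centers (PHCs) equally to the two arms and recruits the providers within them: "the number per PHC will be based on the population of the catchment area of the PHC".

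**The concern.** A repeated-measures analysis with two groups and three time points tests three effects: group, time and group-by-time. They do not share one power figure. Positive correlation between a provider's repeated scores helps the tests of change and hurts the test of the group average. A sample sized for one kind of effect therefore cannot be said to find medium effects of every kind.

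This is the only formal power statement in the article; for patients it says that no sample size calculation was done. A reader who relies on it would credit the study with a sensitivity to average differences between arms that it does not have.

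**Working it through.** **Inputs from the article.** N = 44 (22 per arm), f = 0.25, m = 3 time points, k = 2 groups, two-sided alpha 0.05 (from Data Analysis).

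**Assumed, not in the article.** Correlation between repeated measures r = 0.5 and sphericity (epsilon = 1). They are inferred because they return the stated N. Power comes from the noncentral F distribution.

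**1. Reproducing the stated figure (within-type effects).**

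lambda = N f² m / (1 − r) = 44 × 0.0625 × 3 / 0.5 = 16.5, with (k − 1)(m − 1) = 2 and (N − k)(m − 1) = 84 df.

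Power = 95.6%. N = 42 gives 94.6%, so 44 is the smallest balanced total that reaches 95%. The time main effect has the same lambda and df here, hence the same 95.6%. The multivariate form of the test gives 94.8%, with 46 as its smallest even N. The stated figure stands for effects of this type.

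**2. The group main effect, same inputs.**

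lambda = N f² m / (1 + (m − 1) r) = 44 × 0.0625 × 3 / 2 = 4.125, with 1 and 42 df.

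Power = 51.0%. At r = 0.5, 95% power would take 142 providers (71 per arm).

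**3. Dependence on the unstated r (N = 44, f = 0.25).**

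| r | Group lambda | Group power | Interaction lambda | Interaction power |
|---|---|---|---|---|
| 0 | 8.25 | 80.1% | 8.25 | 71.5% |
| 0.2 | 5.89 | 66.0% | 10.31 | 81.3% |
| 0.3 | 5.16 | 60.2% | 11.79 | 86.5% |
| 0.5 | 4.125 | 51.0% | 16.5 | 95.6% |
| 0.7 | 3.44 | 44.1% | 27.5 | 99.8% |
| 0.9 | 2.95 | 38.9% | 82.5 | >99.9% |

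Group power never reaches 95% in this range. Where it is highest, interaction power is lowest.

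**4. Large group effect, f = 0.40, r = 0.5.** lambda = 44 × 0.16 × 3 / 2 = 10.56 on 1 and 42 df; power 88.8%.

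**5. t test at one time point.** With two equal groups, f = 0.25 is d = 0.5. Noncentrality = 0.5 × √(22/2) = 1.66 on 42 df; power 36.7%.

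**6. Clustering by PHC, group effect only.** Divide the 4.125 by the design effect 1 + (44/J − 1) × ICC, where J is the number of PHCs. The ICC is an assumption, since the article gives none. Results at r = 0.5:

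| J | ICC | Design effect | Power, 42 df | Power, J − 2 df |
|---|---|---|---|---|
| 10 | 0.05 | 1.17 | 45.0% | 38.0% |
| 10 | 0.10 | 1.34 | 40.3% | 34.0% |
| 12 | 0.05 | 1.13 | 46.2% | 40.7% |
| 12 | 0.10 | 1.27 | 42.2% | 37.2% |

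This adjustment does not carry over to the interaction. A level shared by all providers of one PHC cancels from each provider's change over time. In a simulation of 44 providers in 12 PHCs (r = 0.5, f = 0.25, 4,000 runs), interaction power was 95.8%, 95.1% and 95.3% at ICC 0, 0.05 and 0.10.

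**The case against.** The strongest defence is that the calculation is correct and addresses the right effect. Assessments are at enrollment, week 6 and week 12, so a group main effect averages in the enrollment value. With a baseline among the repeated measures, the intervention effect is ordinarily the group-by-time term, and that is a term for which 44 suffices. This stands in part. It means that 51% must not be presented as the power of the trial's arm comparison. It does not rescue the sentence, because the article names no powered effect, claims all of them, and lists direct comparisons of the arms in Data Analysis.

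A second defence is that r and sphericity are settings a condensed article may leave to the full protocol or analysis plan. That is accepted: their absence is not the fault. The fault is a printed statement that is untrue at every correlation examined. Nor does pilot status excuse it, since the article uses that reason only for the patient sample.

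Three stronger readings are tempting but unsupported:

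- That 44 is wrong, or that the power statement fails altogether. It reproduces for the interaction and for time.
- That the 95% holds for the interaction alone. The time effect has the same power; the interaction is simply the only effect involving the intervention that reaches it.
- That allocating PHCs must erode the interaction power as well. It would do so only if PHCs differ in their time trends, and the article gives no information on that.

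The article also does not say that a null arm difference would be read as ruling out a medium effect. That is a risk for readers, not a stated plan.

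**Conclusion.** The concern holds for the breadth of the claim, not for the sample size. Forty-four providers give about 95% power for a group-by-time or time effect of f = 0.25 if r = 0.5 and sphericity holds. They do not give it for every medium effect, and for a large group effect power is also below 95%.

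The conclusion does not hang on r = 0.5, because the group effect falls short of 95% at every r from 0 to 0.9. Only the size of the shortfall depends on r. The further loss from clustering rests on an assumed ICC and on the choice of degrees of freedom; its direction for the group effect is clear, but its size is not known from the article.

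**What to change.** Rewrite the provider paragraph under Sample Size Estimation:

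- State that the 95% applies to a group-by-time interaction of f = 0.25, assuming r = 0.5 between repeated measures and sphericity. The sponsor should first confirm these settings against the saved calculation, since they are inferred here.
- Delete the sentence on uncovering all large and medium effects, or limit it to that interaction.
- Give the power for a group main effect of f = 0.25 as about 51% (39–80% depending on r).
- Note that the calculation treats providers as independent although PHCs are allocated. Clustering would lower group-effect power further, and would lower interaction power only if PHCs differ in their time trends. No clustered interaction figure should be printed without a stated assumption about those trends.

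The cost is one reworded paragraph with less favourable figures. The sample size, design and analysis are unchanged.

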#### Data Analysis

Statistical analyses will be performed using Stata software (version 16, StataCorp). The threshold for statistical analyses will be set at *P*<.05 in a 2-tailed test. We will summarize the baseline data by group assignment using descriptive statistics: means and SDs will be used for continuous data with normal distribution, medians and IQRs for skewed data, and percentages for categorical data. Our primary outcome, number of diagnosed and early detection will be assessed by mix model analysis of variance, with intervention assignment as a between-group factor and time as a within-subject factor. As for continuous data, we will compare the data between control and intervention group using the *t* test or the Wilcoxon Mann-Whitney test. For categorical data, we will compare the data using the chi-square test.

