## Discussion

This paper outlines the protocol for a 3-month pilot trial for evaluating the effect of the eSkinHealth app for the early detection and management of skin NTDs. This app has been our invention, and to our knowledge, there is no other mHealth app of this kind that is developed for the collection of the clinical data of skin diseases in which it can be used both online and offline. It is also portable, and therefore, it can be used in remote communities in LMICs where skin NTDs are endemic and where infrastructure is usually very poor. In terms of teledermatology, while past attempts in using WhatsApp and other social media platforms have shown successful results to an extent [20,21], they do not offer patient health information security. Furthermore, information is exchanged on a one-time basis, and it does not offer a platform for the follow-up of patients. Our system attempts to overcome these challenges.

The outcomes of this study will be primarily assessed by the number of cases of skin NTDs diagnosed and managed using the eSkinHealth app in Côte d’Ivoire, consistent with previous studies in LMICs [30-34]. We will further evaluate it with the SUS score and in-depth interviews. We expect that the average SUS score will be above 68, and the usability of the eSkinHealth app would be considered above average. We hypothesize that the use of the eSkinHealth app will improve the early detection and management of skin NTDs.

Our study may have several limitations. First, although the app can be used offline, an internet connection is required for certain functions. Poor internet connectivity may affect our results. While we can exclude PHCs with known poor internet connectivity, this will form one of the results of our study. We therefore did not include this as our criteria in the selection of the users. Second, the SUS will be evaluated at enrollment, the midpoint (week 6), and the end point (week 12). It is unclear what the effects of the intervention would be if it were prolonged. Lastly, this is a pilot trial involving 10 to 12 PHCs in one or two health districts, and therefore, the study findings may not be generalizable to all health districts in Côte d’Ivoire. These limitations notwithstanding, this study is the first to examine the usability and the effectiveness of the eSkinHealth app to improve the early detection and case management of skin NTDs in Côte d’Ivoire.

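### The primary case number is analysed by ANOVA on arm and time alone, with no population denominator and no named PHC-level unit, although the 10-12 allocated PHCs differ in catchment size

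*Protocol article*

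**What the plan says.** Outcome Measurement defines the phase 3 primary outcome as "differences in case numbers diagnosed and the early detection and follow-up between the intervention group (diagnosis with the app) and the control group". The Discussion restates it as being "primarily assessed by the number of cases of skin NTDs diagnosed and managed using the eSkinHealth app". Both are numbers of cases, not rates.

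Data Analysis fixes the method: "Our primary outcome, number of diagnosed and early detection will be assessed by mix model analysis of variance". The same sentence then names just two terms for this model: "with intervention assignment as a between-group factor and time as a within-subject factor". The threshold is P<.05 "in a 2-tailed test". No offset, catchment covariate, PHC term or pre-trial count is named, and baseline data are only summarised by group.

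Recruitment Procedure makes the PHC the allocated unit: 10 to 12 are selected, and the plan is to "allocate them equally into intervention and control arms". Randomisation is not mentioned. The same section says of the providers that "the number per PHC will be based on the population of the catchment area of the PHC". Sample Size Estimation sets 22 providers per group and cites about 10 registered patients per PHC per month.

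**The concern.** A case number belongs to a PHC over a period. Phase 3 finds cases by active search and at consultation, so the number should rise with the population covered as well as with how well providers detect disease. The plan itself treats catchments as unequal, because it scales provider numbers to them. The named model has no term that takes size out.

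Two things are at stake. Differences in size between PHCs enter the error term and can hide a real effect. If one arm happens to hold larger or more endemic catchments, its total will be higher whatever the app does. A normal-theory model also suits counts poorly, because their variance rises with their mean, but that is the lesser problem. The article expects robust evidence of effectiveness, so the primary contrast should be one that can be interpreted.

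**Working it through.** **The plan's own figure.** No power or sample size is given for the case number. The only power statement concerns 44 providers (f = 0.25, two groups, three times, 95% power). It reproduces for a group-by-time effect, assuming a correlation of 0.5 and sphericity: λ = f²·N·m/(1−ρ) = 0.0625 × 44 × 3/0.5 = 16.5 on 2 and 84 df, power 95.6%. An overall between-group effect at N = 44 would have 51% power. Neither figure describes a comparison of case counts between 10-12 PHCs.

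**Inputs.**
- From the protocol: 10 or 12 PHCs, half per arm; 10 × 3 = 30 cases per PHC in 3 months; two-sided 5%.
- Assumed: catchment CV 0.3 to 0.5, between-PHC CV of the true rate 0.3, true rate ratio 1.5.

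**Spread between PHCs (approximate).** For a raw count, CV² = 1/30 + (1 + CV_catchment²)(1 + CV_rate²) − 1.
- Catchment CV 0.3: 0.033 + 1.09 × 1.09 − 1 = 0.221.
- Catchment CV 0.5: 0.033 + 1.25 × 1.09 − 1 = 0.396.
- Per head of catchment: 0.033 + 0.09 = 0.123 in either case.

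Catchment size thus supplies (0.221 − 0.123)/0.221 = 44% to (0.396 − 0.123)/0.396 = 69% of the squared CV. A denominator removes that part.

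**Apparent difference with no app effect, 12 PHCs.** SD of the log ratio of arm totals ≈ √(2·CV²/6).
- Catchment CV 0.3: √(2 × 0.221/6) = 0.27. Catchment CV 0.5: √(2 × 0.396/6) = 0.36.
- The median absolute difference is exp(0.6745 × SD) − 1, which is about 20% and 27-28%. Simulation gives 20-27%.
- If the arms' total populations are equal, SD ≈ √(2 × [0.09 × (1 + CV_catchment²)/6 + 1/180]) = 0.21 to 0.22, a median of about 15-16%.

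**Power by simulation** (Poisson counts, log-normal catchments and rates, t test across PHCs standing in for the between-arm contrast, rate ratio 1.5; ranges run over catchment CV 0.3-0.5):

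| Setting | Raw PHC counts | Log PHC rates |
|---|---|---|
| 12 PHCs | 15-26% | 43-46% |
| 12 PHCs, equal arm populations | 9-23% | about 45% |
| 10 PHCs | 13-22% | 36-38% |

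Equal arm totals do not rescue the raw-count test. Size still varies between PHCs within each arm and inflates the error term, so the test becomes conservative: its type I error falls to 0.5-1.5%.

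**False positives.** If arms differ in size only by chance, the raw-count test stays near or below 5%. The error rises only under a systematic difference. With 12 PHCs, rate CV 0.2 and one arm's mean catchment 1.5 times the other's, the median raw ratio is about 1.5 with no app effect. The false-positive rate is then 34% (catchment CV 0.3) or 19% (0.5), against about 5% per head of catchment.

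**The case against.** The strongest reply is that the plan already controls for population. Providers per PHC follow catchment population and each group has 22 providers, so total populations may be roughly equal between arms. The subject in the ANOVA may also be the provider, as in the power calculation, and cases per provider would then be close to a rate. With PHC means of cases per provider and equal arm populations, power at 12 PHCs is 40-41%, not far below that of a true rate.

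Part of this stands: arm populations may well be similar. But the split does not remove size variation between PHCs from a raw-count analysis, and it does not balance endemicity. The provider reading rests on a unit that Data Analysis does not name. If 44 providers were treated as independent, clustering within PHCs would give 13-20% false positives (rate CV 0.2-0.3). A group-by-time term would absorb fixed level differences only if the first time point were a pre-intervention case count, and none is defined.

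It is also fair that this is a pilot with no power target for case counts. Low power therefore contradicts nothing stated. It is a reason to prefer the more efficient analysis, not evidence of a broken promise.

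**Conclusion.** The primary analysis is fixed on a poor scale and should be changed. With the assumed CVs, putting PHC counts over population raises power for a rate ratio of 1.5 with 12 PHCs from about 15-26% (9-23% with equal arm populations) to about 43-46%. The figures depend on the CVs, which the protocol does not give. The direction does not, as long as catchments differ.

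Three stronger readings are not supported.
- A reader might infer that the comparison is biased. The protocol is silent on how PHCs were allocated; it does not say that allocation was non-random. Without a systematic difference between arms, the type I error is not inflated.
- A reader might take one SD of the log ratio as the typical chance difference, which gives 30% or more. The median is about 20-27%, or about 15% with equal arm populations.
- A reader might infer that usable pre-trial counts exist, because control-arm cases are reported "using the consultation registry of the Ministry of Health and the skin NTD reporting forms of the World Health Organization". That describes reporting during the trial. It does not show comparable past counts per PHC, and the Introduction notes the lack of a system for patient records.

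**What to change.** Define the phase 3 primary outcome as new cases per catchment population per PHC over the 3 months, using the population figures that already set provider numbers. Name the PHC as the unit of analysis. Use one of two analyses:
- a t test or small-sample regression on PHC rates; or
- negative binomial regression with a log(population) offset and small-sample inference at PHC level.

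These are alternatives, not the same analysis. Log rates need a rule for zero counts, which may arise by disease or by 6-week period. Report the rate ratio with its 95% CI.

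Adjust for a pre-trial PHC case rate only if past registry counts prove available and comparable, given that the trial adds active case finding. Enrolment began in February 2022, so allocation is probably settled: state how PHCs were allocated and, if not at random, describe the comparison as non-randomised.

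The cost is minor rewording of the outcome and the analysis. No new data are needed unless pre-trial counts are sought.

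### The stated 95% power belongs to a time-related effect; the between-arm difference that the primary outcome asks about has about 51% at the same N, and the deciding term is not named

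*Protocol article*

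**What the plan says.** Protocol article, Outcome Measurement: the phase 3 primary outcome is "differences in case numbers diagnosed and the early detection and follow-up between the intervention group (diagnosis with the app) and the control group". The Discussion adds the direction: "We hypothesize that the use of the eSkinHealth app will improve the early detection and management of skin NTDs". Both describe a difference in level between arms.

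Data Analysis: the primary outcome "will be assessed by mix model analysis of variance, with intervention assignment as a between-group factor and time as a within-subject factor". No term of the model is named as the primary test, and the time levels for case counts are not given. For all tests, "The threshold for statistical analyses will be set at *P*<.05 in a 2-tailed test".

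Sample Size Estimation: the provider number comes from a "repeated-measures multivariate analysis of variance (RMANOVA) with three time points and two groups". "An estimated medium effect size of Cohen *f* 0.25 was used to determine the sample size", and at 95% power "a sample size of 44 local health care providers is needed to detect the hypothesized medium-sized effects on the various outcomes". The section then claims that this analysis would find every medium or large effect. It states neither the effect term nor the correlation among repeated measures.

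Phase 2 and Phase 3: intervention providers receive the tablet and app training in phase 2. The same providers register patients "during active case finding and during consultation at PHC throughout the trial period on the eSkinHealth app platform". No case count from before the app is described.

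**The concern.** An arm-by-time design with three time points produces different tests for different questions. The arm effect asks whether the arms differ on average over the period. The interaction asks whether the difference changes over the period. They coincide as tests of treatment only when the first time point precedes the intervention.

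The trial asks the first question. The only power figure for this design has to be attached to one of these tests, and the arithmetic attaches it to the second kind. Two things are at stake:

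- A reader will believe that 44 providers give 95% power for the primary comparison when they do not.
- With the deciding term open, two tests from the same model can give opposite answers on the same data.

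Early detection adds a difficulty. A patient is first detected only once, so at patient level there is no within-subject time for this outcome.

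**Working it through.** **Inputs.** From Sample Size Estimation: N = 44, k = 2 groups, m = 3 times, f = 0.25, target power 95%. From Data Analysis: two-sided 0.05. Not stated and therefore assumed: correlation among repeated measures ρ = 0.5 (range 0 to 0.8 shown) and sphericity ε = 1.

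**Step 1, reproduce the plan's figure.** For the arm-by-time interaction in the usual G*Power form, λ = N f² m / (1 − ρ), with df (k − 1)(m − 1) and (N − k)(m − 1).

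- λ = 44 × 0.0625 × 3 / 0.5 = 16.5; df 2 and 84; critical F 3.11; power 95.6%.
- At N = 42 the power is 94.6%, so 44 is the smallest even N that reaches 95%. The plan's number reproduces.
- With two groups the time effect has the same λ and df, so it reproduces equally.
- The multivariate version of the within-type test gives 94.8% at N = 44 and needs 46, which is the same answer for practical purposes.

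**Step 2, same inputs for the between-arm effect.** λ = N f² m / (1 + (m − 1)ρ), with df k − 1 and N − k.

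- λ = 44 × 0.0625 × 3 / 2 = 4.125; df 1 and 42; critical F 4.07; power 51%.

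| ρ | Within-type power, N = 44 | Between-arm power, N = 44 | N for 95%, between-arm |
|---|---|---|---|
| 0 | 72% | 80% | 72 |
| 0.3 | 86% | 60% | 114 |
| 0.5 | 96% | 51% | 142 |
| 0.8 | >99% | 41% | 184 |

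No correlation from 0 to 0.8 gives the between-arm effect 95% at N = 44; about −0.2 would be needed. At ρ = 0.5, the smallest f detectable with 95% power is 0.45. These figures treat providers as independent. Centers are what is allocated (Recruitment Procedure), so positive clustering by center would lower the between-arm power further.

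**Step 3, what the interaction can see.** This is an illustrative simulation. Taken from the article: 5 to 6 centers per arm and 10 cases per center per month. The article gives the latter for registrations in the app; here it is used as the control mean. Assumed: Poisson counts, three separate monthly counts all under the app, and between-center CV 0.2 to 0.4.

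- App steadily doubles cases: arm effect rejects 58–99%, interaction about 5%, which is its type I rate.
- Steady 1.5-fold effect: arm effect 24–68%, interaction about 5%.

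In a second illustration there were 22 providers per arm, means of 8 versus 12 per period, and a provider SD of 0.3 on the log scale. A constant uplift gave 4.7% for the interaction and 95.6% for the arm effect. When period 1 was made a true pre-app baseline, the interaction rejected 88%. What the interaction tests therefore depends on how time is defined for the counts, which the article does not say.

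**The case against.** The strongest reply is that the Data Analysis section names no interaction. The arm effect is a standard output of the stated model and tests exactly the level difference in the outcome definition. A reader might infer that the planned test answers the wrong question. The documents do not support that, because the deciding term is open rather than wrongly chosen.

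Nor do they establish that a steady effect would be missed. The absence of a pre-app count is an inference from the Phase 2 and Phase 3 descriptions, and no time levels for counts are given. If counts are cumulative from zero at weeks 0, 6 and 12, the interaction rejects about 73–99% under a steady doubling.

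A reader might also infer that a mere shift in timing would usually be declared an effect. That rests on an extreme pattern. Monthly multipliers of 1.5, 1.0 and 0.5 give 78–90% rejection by the interaction (CV 0.2–0.3), but 1.2, 1.0 and 0.8 give only 18–23%.

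The sizing cannot single out the interaction either, because the time effect gives the same number and ρ = 0.5 is assumed. The three defined assessment times belong to the usability scale and survey instruments. For patients, the article says that no calculation was made.

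All of this stands. One could add that naming the deciding term is detail for the full protocol or analysis plan. That does not dispose of the point. The article itself quotes a power for this design, applies it to the outcomes generally, and claims that all medium-sized effects would be found. For the contrast that defines the primary outcome, that statement is wrong.

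**Conclusion.** The point holds as a mismatch between the stated power and the stated primary comparison. The 95% at N = 44 and f = 0.25 belongs to a within-type effect (ρ = 0.5, ε = 1 assumed). The between-arm effect has about 51% on the same assumptions and 41–80% over ρ from 0.8 to 0. The conclusion that it falls short of 95% does not depend on the choice of ρ in that range.

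The insensitivity of the interaction to a steady excess of cases is conditional. It applies if the counts are separate periods, all under the app, and if the interaction is taken as the treatment test. The article fixes neither condition and excludes neither. The matter should be corrected, and the correction is one of wording.

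**What to change.** **Data Analysis.** Define the counting periods and the unit that is counted. Suggested text: *The primary test is the between-arm effect on the total number of cases diagnosed over the 3 months, allowing for PHC. The arm-by-time interaction is exploratory, unless a count from before the app is included as the first time point. Early detection is analysed once per patient, at diagnosis, by arm, allowing for PHC.*

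**Sample Size Estimation.** State that the 95% refers to a within-type effect, and give the correlation assumed. Restate the power for the arm effect: about 51% at f = 0.25 and ρ = 0.5, or a detectable f of about 0.45 at 95% power, in both cases before clustering by PHC. Withdraw the claim that all medium-sized effects would be found, or limit it to the within-type effect.

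**Cost.** No new data and no new software. The downside is a less favourable power figure for the primary comparison, which a pilot trial can report openly.
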